### 2.5. Intervention

Before the intervention allocation is revealed, the monitors/caregivers will receive training on both interventions to ensure that the explanations and implementation are as consistent as possible across all centers.

Both exercise training programs would be performed at the rate of two 60 min sessions per week for three months. After the wash-out period (one month), the training programs will be performed in reverse order for another three months. A follow-up phase of six months is scheduled once the intervention has finished (7 months).

#### 2.5.1. Nordic Walking

Participants will take part in an NW program performed two times a week in 60 min sessions, that will be carried out on non-continuous days, for three months, following previous procedures [15]. Given that any walking technique with poles elicits higher metabolic responses and muscular activation than walking [40], the first four sessions of the program will be focused on learning the NW technique (four sessions of 60 min). Each session will comprise a warm-up of 10 min, a core period (40 min of NW) and a cool-down period of 10 min. The progressive increase in workload will be conducted by an increase in distance and velocity scope (from 2.500 m and 3.75 km/h to 3.500 km and 5.25 km/h) without modifying the core period duration (40 min). In all cases, the intensity of activity will remain less than 75% of the maximal heart rate, a value that will be assessed by means of the equation developed by Fernhall et al. [41]. The NW pole length will be adjusted to the standard formula (0.65 × height) to ensure adequate technique performance.

#### 2.5.2. Fit 5-Fitness Cards

The Fit 5-Fitness Cards program is a structured approach focusing on four key areas of physical fitness: endurance, strength, flexibility, and balance. The sessions include simple exercises tailored to different skill levels, organized into progressive stages (levels 1 to 5) to match the abilities of each participant [18]. Participants will engage in 60 min sessions conducted on non-consecutive days over the course of three months.

The sessions will be led by a graduate in Sport Science with over six years of experience training special populations. Additionally, an instructional video will be provided to support users in performing the exercises during each session. This will ensure consistency across the different centers.

### 2.6. Statistical Analysis

Data will be reported as medians and interquartile ranges for non-normally distributed variables (checked with the Kolmogorov-Smirnoff test) or as means and standard deviations for normally distributed variables. Qualitative variables will be reported as n (%). The intra-cluster correlation coefficient and the cluster-specific effects will also be calculated. Inter-group quantitative variables will be compared, including the primary outcome, with an unpaired, two-tailed t test or the Mann–Whitney U test, as applicable. For inter-group dichotomous data comparison, the two-tailed chi-square tests will be used, with the Yates correction or Fisher’s exact test as appropriate. For repeated measures analysis, the two-way analysis of variance with the Bonferroni correction or the Friedman test, as appropriate, will be used. Comparison will be adjusted by cluster effect. Subgroup analysis of the primary outcome will include sex, age, BMI (normal, overweight and obese), level of physical activity (Inactive, Active), and level of ID (mild, moderate, severe). Multivariate regression models will adjust for confounders such as sex, age, BMI, physical activity, and ID level. Multicollinearity will be checked using the Variance Inflation Factor (VIF), with VIF > 5 indicating high collinearity [42]. Sensitivity analyses will assess robustness. Statistical significance will be set at a two-tailed *p*-value of less than 0.05. All analyses will be conducted using SPSS v24.0 software (IBM Corp., Armonk, NY, USA).

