## 2. Materials and Methods

### 2.1. Study Design

This is a pilot study employing a crossover, cluster-randomized design with repeated measures. This design allows for a within-subject comparison, reducing inter-individual variability and increasing statistical efficiency compared to parallel-group trials, where each subject receives only one treatment [27]. Participating centers will be randomized in a 1:1 ratio into two groups. Two sequential interventions (NW program and Fit 5-Fitness Cards) will be conducted, separated by a 4-week washout period to mitigate potential carryover effects [27]. Following the washout period, the interventions will be repeated in reverse order, adhering strictly to the established protocol. A comprehensive outline of the design and procedures is presented in Figure 1.

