### 2.2. Participants

The sample size was estimated using G*Power (version 3.1., University of Düsseldorf, City, Germany) [28]. A priori power analysis, based on the Wilcoxon signed-rank test, was conducted with an alpha level of 0.05, statistical power of 0.80, and a moderate effect size (Cohen’s d = 0.5). The analysis determined that 67 participants were required. To account for potential dropouts, the final sample size was set at 100 participants, with recruitment evenly distributed across four centers (approximately 25 participants per center). This design ensures robust data collection while allowing for comparative analysis of the interventions.

Participants for this study will be recruited through invitation letters distributed via four associations located across Spain. Eligibility criteria for inclusion in the study are as follows: (a) a confirmed diagnosis of ID arising from neurodevelopmental disorders or autism spectrum disorders; (b) classification of moderate or mild ID (based on a combination of IQ (Intellectual Quotient) scores and adaptive behavior), as defined by the criteria of the Spanish National Health System; and (c) Independent ambulatory ability.

The legal representatives or caregivers of potential participants will be responsible for consulting with the individuals, regarding their willingness to participate in the study and providing written consent on their behalf. Additionally, all participants will have the opportunity to express their own consent or assent regarding their involvement [29].

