#### 2.4.5. Post-Intervention Average Weekly Physical Activity

Before the intervention begins, the participants and their parents will be asked to write the main physical activities (modality and duration) that they usually perform together in a typical week. Once the intervention ends (7 months after the start of the exercise program), a physical activity log will be given to the participants and their parents. They will be asked to register any type of physical activity (modality and duration) performed during a typical week of each month for the following six months.

Four NW poles will be given to the participants (two) and their parents (two) who complete the whole intervention. They will be encouraged to continue practicing NW by themselves for the next six months. Additionally, the registered offices that took part in the research will allow the use of the facilities in which the Fit 5-Fitness Cards and NW program took place at least two days per week, so that the participants and their parents could keep performing Fit 5-Fitness Cards and NW activities, also for the next six months.

Health-related PF, feasibility and QoL measurements will be carried out one week before the start of the training programs (To), once a week after the completion of the first stage (T1), one month later (T2), at the end of the second phase (T3), and six months later (T4). Record logs will be returned at T0 and T4. All the field-based tests and the questionnaire will be administered by the people in charge of the exercise intervention performed in each ID registered office.

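### Section 2.6 tests the primary outcome of a crossover trial with an unpaired test and names no period, sequence or participant term, contrary to the within-person basis of sections 2.1 and 2.2

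*Protocol article*

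**What the plan says.** All references are to the protocol article.

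- **Section 2.1** describes the design: "This is a pilot study employing a crossover, cluster-randomized design with repeated measures". It gives the reason for choosing it: "This design allows for a within-subject comparison, reducing inter-individual variability and increasing statistical efficiency compared to parallel-group trials".
- **Section 2.2** sizes the trial on a paired test: "A priori power analysis, based on the Wilcoxon signed-rank test, was conducted with an alpha level of 0.05", with power 0.80 and d = 0.5. The result is 67 participants, raised to 100 for dropout, in four centres of about 25.
- **Section 2.3** sends Group A through NW and then Fit 5, and Group B through the reverse order.
- **Section 2.6** assigns the primary outcome to an unpaired test: "Inter-group quantitative variables will be compared, including the primary outcome, with an unpaired, two-tailed t test", with Mann–Whitney as the alternative. It adds a two-way analysis of variance or a Friedman test for repeated measures, with no factors named. It promises an adjustment for cluster without a method, and regression models with sex, age, BMI, activity and level of disability. No period, sequence or participant term appears.

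**The concern.** In a two-period crossover each person supplies an NW value and a Fit 5 value. The efficiency that section 2.1 claims comes from differencing the two within the person, and a period term keeps a time trend out of the programme contrast. An unpaired test on the scores themselves does neither.

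The test is attached to the primary outcome by name. A later analysis plan that followed this sentence would inherit a test that does not match the design. At stake are the power, standard error and confidence interval of the main result and, if the sequences end up unequal in size, some bias.

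**Working it through.** **Inputs.** From section 2.2: "an alpha level of 0.05, statistical power of 0.80", d = 0.5, 67 required, 100 planned. From section 2.6, sidedness: "Statistical significance will be set at a two-tailed" threshold. Assumption: the within-person correlation r is not in the documents, so I use 0.3, 0.5, 0.7 and 0.8. Clustering is ignored throughout.

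**1. The plan's own figure.** Rank tests are handled by the noncentral t with relative efficiency 3/π (normal data).
- Signed-rank: m = N × 3/π, df = m − 1, noncentrality d√m. N = 34 gives power 0.788. N = 35 gives m = 33.4, noncentrality 2.89 and power 0.801. The stated inputs therefore need **35**, not 67. At N = 67 the power is 0.976.
- Mann–Whitney, n per group: m = n × 3/π, df = 2m − 2, noncentrality d√(m/2). n = 66 gives 0.795. n = 67 gives m = 64.0, noncentrality 2.83 and power 0.801. So **67 is the per-group Mann–Whitney number**, 134 in all.

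**2. Form (a): Group A against Group B at one visit**, d = 0.5 SD of the scores, Mann–Whitney.
- 67 people (33.5 per group): m = 32.0, noncentrality 2.00, power 0.50.
- 100 people (50 per group): m = 47.7, noncentrality 2.44, power 0.68.

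**3. Form (b): NW and Fit 5 scores pooled as two independent samples of N**, effect 0.5 SD of the within-person differences.
- True standard error: σ√(2(1 − r)/N). The unpaired test uses σ√(2/N), too large by 1/√(1 − r).
- Power ≈ 1 − Φ(c/√(1 − r) − 0.5√N), with c = 1.978 at N = 67 and 1.972 at N = 100.
- Example, N = 67, r = 0.5: 1.978 × 1.414 − 4.093 = −1.296, power 0.90.
- Actual type I error ≈ 2[1 − Φ(c/√(1 − r))].

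| r | SE ratio | Power, N = 67 | Power, N = 100 | Type I error, N = 67 |
|---|---|---|---|---|
| 0.3 | 1.20 | 0.96 | above 0.99 | 0.018 |
| 0.5 | 1.41 | 0.90 | 0.99 | 0.005 |
| 0.7 | 1.83 | 0.68 | 0.92 | 0.0003 |
| 0.8 | 2.24 | 0.37 (0.38 simulated) | 0.72 | below 0.0001 |

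A paired t test has power 0.98 at N = 67 and above 0.99 at N = 100, whatever r is.

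**4. Period effect in form (b).** A shift P in the second period biases NW minus Fit 5 by P × (nB − nA)/N. With equal sequences this is zero. At 55/45 it is a tenth of P.

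**5. An unpaired form that would be valid.** Take each person's first-period minus second-period difference and compare the sequences. The means differ by twice the programme effect, which is 2 × 0.5 = 1.0 SD of the differences. At 33/34 the noncentrality is √(33 × 34/67) = 4.09, power 0.98. At 27/40 it is √(27 × 40/67) = 4.01, power also 0.98. A common period effect cancels.

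**The case against.** The best defence is step 5: an unpaired test between Groups A and B is a standard crossover analysis when the variable is the within-person period difference. Section 2.6 does not define the variable tested, and the article condenses a fuller protocol. This stands in part: the text does not show that a wrong analysis must follow. But the article describes a comparison of quantitative variables between groups and mentions no period differences, so it still contradicts sections 2.1 and 2.2 as written.

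A reader might also infer several stronger things that the documents do not support:

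- **That a cluster adjustment is impossible here.** Cluster-adjusted t tests and clustered rank-sum tests exist, and section 2.6 says the intra-cluster correlation will be calculated. Only the method is unstated.
- **That the repeated-measures analysis is known to be wrong.** Its factors are not named. It is simply not assigned to the primary outcome, and a Friedman test cannot carry sequence or period.
- **That false positives are inflated.** With positive correlation, ignoring the pairing makes form (b) conservative. In form (a) ignoring the pairing causes no standard-error fault, and a common time trend cancels.
- **That power always collapses.** With all 100 retained, form (b) stays above 80% for r up to 0.7.
- **That the number 67 rests on pairing.** Only the wording does (step 1).

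**Conclusion.** The point holds as a contradiction within the article: a within-person design and a stated paired power basis, but an unpaired primary test with no period, sequence or participant term.

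If the test is done at one visit, power at d = 0.5 is about 50% to 68%, below the stated 80% even without dropout. If scores are pooled, the standard error is 1.2 to 2.2 times too large over the assumed correlations. The loss of power then runs from slight (r = 0.3) to severe (r = 0.8 at N = 67), and a period effect biases the result only if the sequences are unequal.

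These sizes rest on assumed correlations, normal data and no clustering. The contradiction does not depend on them. It governs the main result and should be settled before analysis.

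**What to change.** In section 2.6, replace the unpaired test for the primary outcome with one prespecified within-person analysis that includes period. Either form will do:

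- a mixed model on the T1 and T3 scores, with programme, period and sequence as fixed effects and participant as a random effect; or
- a test of within-person period differences between the two sequences, stated as such.

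Account for centre in a way suited to four clusters: a simple centre term, or a centre-level summary with small-sample degrees of freedom. Four centres give eight centre-by-period cells. After the mean, centre, period and programme, 8 − 1 − 3 − 1 − 1 = 2 degrees of freedom remain (t critical value 4.30), so separate centre and centre-by-period variances should not be fitted unless they prove estimable.

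Report NW minus Fit 5 with a 95% CI. The introduction words the primary objective as the effect of NW alone, so state that this is the contrast tested. Correct section 2.2 to match the chosen analysis.

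A separate point needs settling before T2 serves as a period baseline. Section 2.4.5 places the visits "once a week after the completion of the first stage (T1), one month later (T2), at the end of the second phase (T3"). Read literally, with T1 a week after stage one and a 4-week washout (section 2.1), T2 falls about a week into the second programme. It may simply mean the end of washout, and the two passages must be reconciled.

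The cost is rewording, with no new data. The cluster-adjusted interval will be wider.

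### The primary outcome of this cluster-randomised crossover is assigned an unpaired test, in conflict with the within-person rationale of the design and the paired test used to size it

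*Protocol article*

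**What the plan says.** Section 2.1 describes the design: "This is a pilot study employing a crossover, cluster-randomized design with repeated measures". It gives the reason for choosing it: "This design allows for a within-subject comparison, reducing inter-individual variability and increasing statistical efficiency compared to parallel-group trials". Section 2.2 sizes the trial accordingly: "A priori power analysis, based on the Wilcoxon signed-rank test", with "alpha level of 0.05, statistical power of 0.80" and Cohen's d of 0.5. This gives 67 participants, raised to 100 across four centres.

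Section 2.6 then sets the test for the primary outcome: "Inter-group quantitative variables will be compared, including the primary outcome, with an unpaired, two-tailed t test", with a Mann–Whitney U test as the alternative. Two further sentences in that section bear on the point. One reads "For repeated measures analysis, the two-way analysis of variance with the Bonferroni correction or the Friedman test, as appropriate, will be used". The other reads "Comparison will be adjusted by cluster effect". Neither mentions the primary outcome. The factors of the analysis of variance and the method of cluster adjustment are not given.

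**The concern.** In a two-period, two-sequence crossover, the programme effect is estimated from each person's own difference between periods. An unpaired test fits that design only if it is applied to those differences and compares the two sequences. Section 2.6 speaks of quantitative variables and does not mention differences.

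The article supports two plain readings of the word group. In section 2.3 the groups are the sequences, A and B. In the cost-effectiveness formulas of section 2.4.4 they are the programmes, NW and Fit 5.

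- **Programme reading:** the same people are treated as two independent samples.
- **Sequence reading:** the test is a parallel-group comparison at one visit, and the programme contrast changes sign between T1 and T3.

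On either reading the primary p-value and interval do not match the design. A programme difference that the crossover could detect may be reported as no difference. The two readings also give different answers, so the primary result is not fixed in advance.

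**Working it through.** **Inputs from the article:** 67 participants required and 100 recruited; four centres of about 25; d = 0.5 on an unstated scale; two-sided 0.05; power 0.80. **Assumed, because the article gives no value:** within-person correlation ρ of 0.5, 0.7 or 0.9; normal outcomes with SD 1 in each period; no centre effect until step 6.

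**1. The plan's own figure.** I used noncentral-t power with the sample size scaled by the relative efficiency 3/π. The two-sided signed-rank test at d = 0.5 then needs 35 people, not 67. No one- or two-sided variant with another parent distribution gives 67 (range 18 to 39). The two-sample Mann–Whitney test gives exactly 67 per group, 134 in total. So the named test is paired, but the figure matches an unpaired per-group size. How it arose cannot be told from the article.

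**2. Programme values treated as independent: standard error.** Unpaired SE = √(2/N). Correct SE = √(2(1−ρ)/N). The ratio is 1/√(1−ρ):
- ρ = 0.5: 1/√0.5 = 1.41
- ρ = 0.7: 1/√0.3 = 1.83
- ρ = 0.9: 1/√0.1 = 3.16

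True type I error = 2[1 − Φ(1.96/√(1−ρ))], which is 0.6% at ρ = 0.5, 0.04% at 0.7 and effectively zero at 0.9.

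**3. Effect-size scale.** If 0.5 is in SDs of the within-person difference, the raw effect is 0.5·√(2(1−ρ)) = 0.500, 0.387, 0.224. If 0.5 is in between-person SDs, the raw effect stays at 0.5 and the standardised paired effect is 0.5/√(2(1−ρ)) = 0.500, 0.645, 1.118.

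**4. Power with 67 people** (t tests; pooled figures by simulation, T1 figures from the noncentral t):

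| Scale of d | ρ | Paired | Programmes as independent samples | A v B at T1 (34 v 33) |
|---|---|---|---|---|
| Within-person | 0.5 | 0.98 | 0.90 | 0.52 |
| Within-person | 0.7 | 0.98 | 0.68 | 0.35 |
| Within-person | 0.9 | 0.98 | 0.03 | 0.15 |
| Between-person | 0.5 | 0.98 | 0.90 | 0.52 |
| Between-person | 0.7 | >0.99 | 0.95 | 0.52 |
| Between-person | 0.9 | >0.99 | 0.995 to 0.996 | 0.52 |

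With all 100 people, the T1 comparison (50 v 50) has power 0.70, 0.48 and 0.20 on the within-person scale, and 0.70 throughout on the between-person scale.

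**5. The form that would suit the design.** Take period 1 minus period 2 for each person and compare sequences. The sequence means differ by twice the programme effect, which is 2 × 0.5 = 1.0 SD of the difference. With 34 v 33, power is 0.98, so removing a common period effect costs almost nothing.

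**6. Centres.** Sequence is randomised to four centres, two per sequence. If step 5 is analysed by participant and the period differences have a centre ICC of 0.01 (assumed), simulated type I error is 7 to 8% with 17 or 25 per centre. At 0.05 it is 15 to 19%. Comparing centre means (two v two) restores 5%, but the t critical value on 2 degrees of freedom is 4.30. With no centre variance, the SE of the sequence difference is 1/√m SDs for m people per centre. The noncentrality is therefore √17 = 4.12 or √25 = 5, and power is 0.59 or 0.72.

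**The case against.** The strongest defence is that section 2.6 does contain a within-person element. The Friedman test ranks within person, a two-way analysis of variance could include period, and a cluster adjustment is promised. It is therefore too much to say that the plan abandons within-person analysis. But the primary outcome is named under the unpaired test and nowhere else. The Friedman test has no sequence or period term, so it does not separate the programmes from a period effect. Adjusting for centre does not restore pairing within a person.

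A second defence is that an unpaired test between Groups A and B could mean a test of period differences, which is the standard crossover test. The wording does not exclude this, but it does not say it either, and the plainest readings are the other two. A statistical analysis plan may exist and settle the matter. The conflict nevertheless lies in what the article itself states, so it is not a detail merely left to another document.

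A reader might infer that the standard errors are wrong in every case and that most of the design's power is lost. The document does not support either. A one-visit comparison of sequences has a valid standard error apart from clustering; it is only inefficient. The loss depends on a correlation the article does not give and on an effect-size scale it does not state. At ρ = 0.5 the pooled unpaired test loses about 8 points (0.98 to 0.90), and on the between-person scale it loses less at higher ρ.

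**Conclusion.** The point stands as a contradiction between section 2.6 and sections 2.1 and 2.2: the test named for the primary outcome is unpaired, while the design rationale and the named sizing test are paired. It should be corrected before analysis because it concerns the primary test itself.

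The consequence depends on how the sentence is applied. Comparing programme values as independent samples overstates the standard error by 1/√(1−ρ) and, at ρ of 0.5 or more, holds type I error below 1%. Comparing sequences at T1 leaves power at 0.52 or lower with 67 people over the range of ρ examined. The size of the pooled power loss is not established: it runs from negligible to nearly total over the assumed correlations and the two scales. All the paired benchmarks of 0.98 or more assume no centre effect, and with four randomised centres the trial may not reach them.

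**What to change.** Replace the unpaired test as the primary analysis with one that keeps the pairing. Either of these would do:

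- For each participant, take the outcome after period 1 minus the outcome after period 2 and compare this between Group A and Group B. Half the between-sequence difference estimates NW minus Fit 5, free of a common period effect.
- Fit a mixed model with programme and period as fixed effects and participant as a random effect.

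In both cases, allow for the unit of randomisation: include centre and centre-by-period effects with a small-sample correction, or analyse centre-level summaries. A participant-level analysis without this could replace a conservative test with an anti-conservative one. Report NW minus Fit 5 with its 95% interval. Keep unpaired tests of raw values for baseline description, and state what the analysis of variance or Friedman test is for. The sample-size statement should then name the same analysis and the scale of d.

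The cost is one paragraph of wording and no new data. The four-centre correction widens the interval and lowers power, as step 6 of the working shows. People with only one period contribute less: the mixed model can still use them, but the difference-based test cannot.

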Regarding the Fit 5-Fitness Cards, the limited existing research has demonstrated their effectiveness in improving body composition and metabolic health among Special Olympic athletes [19]. However, only one study appears to have been conducted specifically with individuals with ID. In the study by Ptomey et al. [26], the Fit 5-Fitness Cards were utilized to promote physical activity among adults with ID as part of a comprehensive weight management intervention. This highlights the clear need for further research to evaluate the efficacy of this strategy in individuals with ID.

Therefore, the primary objective of this study is to evaluate the effect of the NW program on the QoL and functionality of individuals with ID. Additionally, the secondary objectives include assessing the impact of the Fit 5-Fitness Cards program on QoL and functionality, as well as comparing the safety, feasibility, and adherence of these two alternative exercise interventions.

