### 2.3. Procedures

The registered sites will be randomly assigned to two groups using a random number table generated in Excel. The randomization process will be unrestricted, with no stratification or pairing of sites. To minimize selection bias, allocation concealment will be ensured by having an independent researcher generate the randomization sequence and store it in a secure file. Following the recruitment of the participating sites and the completion of the training period for monitors/caregivers, the randomization table will be unblinded, and the sites will be allocated to one of two groups. Preferably, the monitors/caregivers will be occupational therapists, physiotherapists, or social workers with specialized training in adapted exercise.

Group A will initially implement the NW program, followed by the Fit 5-Fitness Cards program. Conversely, Group B will undertake the programs in the reverse order. The random sequence will be generated by [name], while [name] will be responsible for informing the registered sites of the exercise sequence their members are required to follow.

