#### 2.4.3. Feasibility of the Programs

The following variables would be recorded by the people who will administer the exercise programs to assess their feasibility: recruitment rate (number of participants recruited from those that fulfilled the inclusion criteria) [35]; attrition (number of drop-outs); completion rate (number of participants who completed each outcome measure); adherence measurement with comprehensive reporting [36] (proportion of participants with participation rates exceeding 80%); participation (total of exercise hours completed divided by the total number of possible hours); and safety and tolerability (number of participants who experienced exercise-related adverse effects, such as pain, dizziness, intense fatigue, falls, etc., resulting from exercise performance). Participants may experience some discomfort, fatigue, or muscle soreness, which are common among sedentary individuals starting a physical activity intervention. However, these effects typically diminish after two or three sessions [37].

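### Only independent-groups tests are named for yes/no outcomes, although every participant is observed under both programmes, so the programme comparison of adherence, completion and adverse effects does not hold its 5% level

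*Protocol article*

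**What the plan says.** All references are to the protocol article.

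- **Design (2.1).** "This is a pilot study employing a crossover, cluster-randomized design with repeated measures". The stated advantage is that "This design allows for a within-subject comparison, reducing inter-individual variability and increasing statistical efficiency compared to parallel-group trials".
- **Order (2.3).** "Group A will initially implement the NW program, followed by the Fit 5-Fitness Cards program"; Group B takes them the other way round. Each participant is therefore observed under both programmes.
- **Objective (1, repeated in 4).** A secondary aim is "comparing the safety, feasibility, and adherence of these two alternative exercise interventions".
- **Outcomes (2.4.3).** Adherence is the "proportion of participants with participation rates exceeding 80" per cent. Completion of each measure and exercise-related adverse effects are counts of participants. All three are yes/no for each person.
- **Tests (2.6).** "For inter-group dichotomous data comparison, the two-tailed chi-square tests will be used, with the Yates correction" or Fisher's exact test. The repeated-measures sentence offers a two-way analysis of variance or the Friedman test, neither of which is put forward for paired binary data. A further sentence promises adjustment for the cluster effect and names no method.

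**The concern.** Pearson, Yates-corrected and Fisher tests take the two columns of the table to be different people. Here they are the same people twice. The word inter-group can be read in three ways, and none gives a sound programme comparison:

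1. **Nordic Walking against Fit 5, both periods.** The pairing is ignored.
2. **Group A against Group B, both periods.** Each group contains both programmes, so the test compares sequences and does not address the objective.
3. **Group A against Group B, first period only.** Pairing is no longer an issue, but half of the crossover is discarded and whole centres are being compared.

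At stake is whether the stated comparison of safety, feasibility and adherence has a known error rate, and whether it uses the within-subject efficiency that the design is said to offer.

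**Working it through.** **Inputs from the protocol article.** Two-sided 5% level (2.6). 67 participants required and 100 planned, about 25 in each of four centres (2.2). The plan gives no sample size, power or expected rates for binary outcomes, so there is no figure to reproduce. The 67 serves here only as the number of completed pairs.

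**Assumptions, not in the documents.** Within-person correlation phi, event rates, and intraclass correlations (ICC).

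**1. Error rate when pairing is ignored, no clustering.** With common rate p and n pairs, the test uses variance 2p(1−p)/n for the difference. The true variance is 2p(1−p)(1−phi)/n. The error rate is therefore about 2·[1 − Φ(1.96/√(1−phi))].

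- phi 0: 1.96/1 = 1.96, giving 5.0%
- phi 0.3: 1.96/0.837 = 2.34, giving 1.9%
- phi 0.5: 1.96/0.707 = 2.77, giving 0.6%

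Simulation at n = 67 with 70% in both programmes agrees. With Yates, rejection is 1.0% to 0.3% over phi 0.3 to 0.5. Uncorrected McNemar stays close to 5%; exact McNemar runs at about 3%.

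**2. Power, 60% against 75%, n = 67, no clustering.**

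- Chi-square standard error: √(2 × 0.675 × 0.325/67) = 0.0809, so the observed difference must exceed 1.96 × 0.0809 = 0.159.
- True standard error: √{[0.24 + 0.1875 − 2·phi·√(0.24 × 0.1875)]/67} = 0.0669 at phi 0.3 and 0.0567 at phi 0.5.
- Chi-square power: 1 − Φ((0.159 − 0.150)/0.0669) ≈ 45% at phi 0.3, and about 44% at phi 0.5.
- Uncorrected McNemar power: Φ(0.15/0.0669 − 1.96) = Φ(0.28) ≈ 61%, and Φ(0.15/0.0567 − 1.96) = Φ(0.69) ≈ 75%.

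Simulation gives:

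| Test | phi 0.3 | phi 0.5 |
|---|---|---|
| Chi-square | 45% | 44% |
| Yates | 37% | 35% |
| Exact McNemar | 51% | 67% |
| Uncorrected McNemar | 61% | 75% |

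**3. Rare events, low correlation.** For 5% against 15%, phi 0.1, n = 67, power is 51% for chi-square, 51% for uncorrected McNemar and 42% for exact McNemar. Here pairing gains almost nothing.

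**4. Adding centre-by-period clustering.** 68 participants in four centres, 70% in both programmes, phi about 0.28, assumed latent centre-by-period ICC. Rejection rates under no difference:

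| ICC | Chi-square | Yates | Exact McNemar |
|---|---|---|---|
| 0 | 2.1% | 1.1% | 3.0% |
| 0.05 | 6.7% | 4.9% | 8.4% |
| 0.10 | 12.7% | 9.5% | 14.7% |

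The conservatism of step 1 can therefore disappear or reverse. Exact McNemar is above the chi-square in every row.

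**5. First period only.** With two centres of 25 in each group, the design effect is 1 + 24 × ICC, that is 1.24, 2.2 and 3.4 at ICC 0.01, 0.05 and 0.10. Simulated error of the unadjusted chi-square is 8%, 19% and 30%.

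**The case against.** The strongest reply is that Section 2.6 never says that adherence, completion or adverse effects will be tested by chi-square. It also says that qualitative variables are reported as counts and percentages, and Section 2.4.3 names no test. The only groups that Section 2.3 defines are the sequence groups, so the sentence could be meant for Group A against Group B at baseline. That stands as a limit: the link is an inference. It is a reasonable one, because the article sets a between-programme comparison of these outcomes and names no other test for binary data.

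Second, the plan promises adjustment for cluster effect, so a plain chi-square is not the whole stated analysis. This is true, and steps 1, 2, 4 and 5 describe the unadjusted tests. But that sentence concerns centres; it does not deal with two results from one person.

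Third, a reader might infer that the planned test will tend to hide a real difference in adverse effects. The documents do not support so firm a direction. They give no within-person correlation, the loss is negligible at low correlation (step 3), and clustering can turn the error the other way (step 4).

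Fourth, these are secondary outcomes in a self-described pilot. That limits the weight of the point but does not remove it. The quantitative sentence in 2.6 has the same fault, with an unpaired t test or Mann–Whitney test, but correcting it would leave the binary outcomes without a suitable method.

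**Conclusion.** The point holds in this form: the only binary tests named assume independent groups, and on none of the readings do they compare the programmes with a known 5% error rate in this clustered crossover.

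The size depends on assumptions. With no clustering and phi from 0 to 0.5, the chi-square error rate falls from 5.0% to 0.6%. At phi 0.3 to 0.5, its power for 60% against 75% is 6 to 23 percentage points below exact McNemar (45% against 51%; 44% against 67%). At phi near zero the loss vanishes. With an assumed centre-by-period ICC of 0.05 to 0.10, the uncorrected test exceeds 5%.

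Two stronger statements should not be made: that the plan expressly assigns chi-square to these outcomes, and that the safety comparison is biased towards finding nothing. The change is worth making before analysis, as a correction to secondary analyses.

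**What to change.** In Section 2.6, for comparisons of the two programmes on binary outcomes, replace the chi-square/Fisher sentence with a mixed-effects or GEE logistic model that has programme, period and sequence terms, a participant effect and centre. Report the within-participant risk difference with its 95% CI.

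Do not make plain McNemar the main analysis: it ignores period and centre (step 4).

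State that four centres limit any cluster-level inference. If they split two and two, a centre-level comparison of period differences has only 4 − 2 = 2 degrees of freedom.

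Keep chi-square/Fisher for describing Group A against Group B at baseline, and name the outcomes to which each method applies.

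The cost is analysis wording only; no new data are needed.
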